| | Inclusion Criteria: | | --- | | |  | 1. Be English-speaking volunteers who are not seeking treatment at the time of the study; 2. Be between 18-55 years of age; 3. Meet DSM-IV TR criteria for cocaine dependence; participants may or may not meet criteria for nicotine dependence. Nicotine dependence is allowed but not required because most cocaine users smoke cigarettes. 4. Have a self-reported history of using cocaine by the smoked or IV route; 5. Have vital signs as follows: supine blood pressure > 100/65 mm Hg, a seated blood pressure of > 90/60 mm Hg and < 150/90 mm Hg, and an orthostatic change < 20 mm Hg systolic or <10 mm Hg diastolic on standing. Resting pulse must be < 90 bpm. 6. Have hematology and chemistry laboratory tests that are within normal (+/- 10%) limits with the following exceptions: a) liver function tests (total bilirubin, ALT, AST, and alkaline phosphatase) < 3 x the upper limit of normal, and b) kidney function tests (creatinine and BUN) within normal limits; 7. Have a baseline EKG that demonstrates clinically normal sinus rhythm, clinically normal conduction, and no clinically significant arrhythmias; 8. Have a medical history and brief physical examination demonstrating no clinically significant contraindications for study participation, in the judgment of the admitting physician and the principal investigator. | | --- | --- | | |

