| | Exclusion Criteria: | | --- | | |  | 1. Meet DSM IV TR criteria for dependence on drugs other than cocaine or nicotine. 2. Have any history or evidence suggestive of seizure disorder or brain injury; 3. Have any previous medically adverse reaction to cocaine, including loss of consciousness, chest pain, or epileptic seizure; 4. Have neurological or psychiatric disorders, such as: • psychosis, bipolar illness or major depression as assessed by MINI; • organic brain disease or dementia assessed by clinical interview; • history of any psychiatric disorder which would require ongoing treatment or which would make study compliance difficult; • history of suicide attempts within the past year and/or current suicidal ideation/plan; 5. Have evidence of clinically significant heart disease or hypertension, as determined by the PI; 6. Have evidence of untreated or unstable medical illness including: neuroendocrine, autoimmune, renal, hepatic, or active infectious disease; 7. Have symptomatic HIV or are taking antiretroviral medication; 8. Be pregnant or nursing. Other females must either be unable to conceive (i.e., surgically sterilized, sterile, or post-menopausal) or be using a reliable form of contraception (e.g., abstinence, birth control pills, intrauterine device, condoms, or spermicide). All females must provide negative pregnancy urine tests before study entry, upon hospital admission, and at the end of study participation; 9. Have asthma or currently use theophylline or other sympathomimetics; 10. Have any other illness, condition, or use of psychotropic medications, which in the opinion of the PI and/or the admitting physician would preclude safe and/or successful completion of the study.  Criteria for Discontinuation Following Initiation Participants will be discharged if they have a positive breath test indicating use of alcohol or a urine test indicating illicit use of drugs while in the MED-VAMC, if they do not comply with study procedures, or if they do not tolerate the study drugs. Stopping criteria are detailed below.  Stopping Criteria Cocaine administration will not be initiated if there are clinically significant arrhythmias or if vital signs are outside of acceptable ranges, which are resting pulse < 130 bpm and blood pressure below 165mm Hg systolic and 100mm Hg diastolic. In addition, repeated doses of cocaine will not be administered (and the study physician will halt continued cocaine delivery) if there are behavioral manifestations of cocaine toxicity (agitation, psychosis, inability to cooperate with study procedures).   Stopping Criteria for Further Participation Subject participation will be terminated if any of the following events occur: 1. Systolic BP greater than 180 mm Hg sustained for 5 minutes or more; 2. Diastolic BP greater than 120 mm Hg sustained for 5 minutes or more; 3. Heart rate greater than (220 – age x 0.85) bpm sustained for 5 minutes or more. Note: if a single value exceeding the values above is detected, the readings will be repeated until it is determined whether or not the stopping criteria have been met.  Subject Selection Criteria Rationale Route of administration. Participants are required to have used cocaine by the IV or smoked route to avoid exposing participants to drugs by routes of administration that produce more intensive interoceptive effects than usually used by the participants. Prior experience with smoked cocaine is allowed (rather than restricting the population to those with experience with IV cocaine) because smoked cocaine reaches brain sites of action as rapidly as does intravenously administered cocaine and smoked cocaine produces effects that are comparable to IV cocaine. Speed of administration (and rate of delivery to brain) of stimulant drugs likely impacts subjective and cardiovascular effects, so smoked and intravenously administered cocaine produce similar subjective effects (22-26). | | --- | --- | | |

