| F2.  Procedure |
| |  | | --- | | |  | Screening Interested candidates will receive an explanation of the study purpose and requirements. If still interested, the candidates will be allowed to review, inquire about, and sign the study informed consent form. After providing informed consent, subjects proceed to the screening assessment phase of the study. A urine drug toxicology screen will be conducted for drugs of abuse. Some of this sample will be shared with Rice university to develop new tests for drug detection. A saliva sample will also be collected for this purpose. Candidates deemed eligible based on initial screening assessments will be administered a MINI by a trained mental health professional, to determine if there are any psychiatric conditions that might exclude the potential subject from participation. Blood will be collected for analysis of hematology and chemistry tests. These assessments must be completed within 14 days before intake. At the initial screening visit, restrictions on use of alcohol, drugs of abuse, and medications will be reviewed. All subjects will be required to sign a written statement that they will abstain from use of cocaine or other psychostimulants throughout the duration of their participation in the trial.  All applicants for study participation will receive counseling as part of their participation, and will be advised that treatment for drug abuse is indicated and available. Applicants not participating in the study will receive treatment referral information as appropriate. At completion of their participation, study subjects will again be advised that treatment is indicated and available, and will be given treatment referral information and assistance.  Participants will reside on the Research Commons for the duration of the study (about 28 days total). Participants must refrain from illicit and prescription drug use, and we will confirm compliance by urine testing and breath alcohol level testing. Passes and monitoring. Passes will not usually be allowed, and visitors will not be permitted. Participants’ belongings will be searched upon arrival.  The study schedule outlined below may change by a day or two due to scheduling issues and/or safety reasons. We will ask participants to complete the protocol twice (once being randomized to placebo and once being randomized to doxazosin, but this wont be required.   General Procedures: Participants will be studied while residing on the Research Commons. Cocaine administration sessions will be conducted at approximately the same time of day for a given participant. Experimental sessions will be several hours in duration and will be conducted in a quiet room with research and medical staff present. The room will contain an experimental station, equipped with a response console attached to a personal computer and video monitor. Heart rate, EKG, and blood pressure will be recorded throughout experimental sessions using an automatic monitoring system.   Smoking, caffeine, and food. Caffeine and food will be prohibited during and 90 min before study sessions excepting a 1 hour break for lunch.   Day 1-10: The study participants will be randomized to receive either doxazosin or placebo. Doxazosin treatment will begin at 1mg and will be increased by 1mg increments every three days until 4mg is reached. Placebo will be dosed identically. Prior to dosing doxazosin, and at 1 hour intervals after each dose from hours 2 through 6 after dosing, sitting and supine orthostatic blood pressure will be assessed.  Cardiovascular monitoring and discontinuation criteria For doxazosin to be administered, the following criteria must be met: 1. supine blood pressure above 100/65 mm Hg, 2. a seated blood pressure of above 90/60 mm Hg, 3. and an orthostatic change smaller than 20 mm Hg systolic or smaller than 10 mm Hg diastolic on standing. The dose will not be increased until the participant has met criteria for dosing and has received 3 doses at a given dose level.  a. Participants who do not meet the criteria above at any time during hours 2 through 6 after dosing will remain supine until the next BP assessment. b. Participants who do not meet the criteria above consistently from hours 2 through 6 after any dosing will not have their dose of doxazosin increased and will remain at the prior dosing level. c. Participants who do not meet the requirements for dosing increase (supine blood pressure > 100/65 mm Hg, a seated blood pressure of > 90/60 mm Hg, and an orthostatic change < 20 mm Hg systolic or <10 mm Hg diastolic on standing) for 6 days will have medication discontinued and they will be discontinued from the study.   Day 10: Cocaine 20mg, 40mg and matched placebo saline will be administered via IV push by the study physician on day 10, at hourly intervals, with the placebo dose randomly interspersed to maintain the blind. To ensure that subjects will not be at risk from cocaine, the resting pulse must be < 90 bpm and the blood pressure must be < 150 mmHg systolic and < 90 mmHg diastolic immediately prior to dosing. Heart rate and blood pressure measurements will be made prior to cocaine dosing and at 15-minute intervals thereafter until 30 minutes following the final dose. Visual-analogue scale ratings of “any cocaine effect”, “high”, “good effects”, “bad effects”, “like cocaine”, “desire cocaine”, “depressed”, “anxious”, “stimulated”, and “if you had access to cocaine right now, how likely would you be to use it?” will be collected at -15 min, 5 min, 10 min, 15 min, 20 min, 30 min, and 45 min after cocaine dosing. Participants will remain seated during experimental sessions except for brief visits to the lavatory.   All infusions will be administered in single-blind fashion. All experimental procedures will be conducted in a hospital room located in the GCRC. Infusions will be administered over 2 minutes by I.V. push. Vital signs must remain within values specified under Stopping Criteria for initiation of cocaine administration. An ACLS-certified physician will be present from 15 min before drug administration until at least 1 hour after cocaine administration. The physician will be available in house and on pager for at least 4 hours after drug administration. Heart rate will be measured using continuous ECG from 15 min prior to cocaine or placebo dosing until 2 hours after dosing. Blood pressure will be assessed at frequent intervals from 15 min prior to cocaine or placebo dosing until 2 hours after dosing.   Discharge Participants will be monitored for stability on days 11 and 12 and discharged from the hospital on day 13. Discharge will only occur for subjects who have a supine BP of 100/65 mm Hg or higher, a seated blood pressure of 90/60 mm Hg or higher, and an orthostatic change upon standing of < 20 mm Hg systolic or < 10 mm Hg diastolic. Prior to discharge subjects will have a physical examination and vital signs, and complete the Beck Depression Inventory-II. An assessment of adverse events will be completed.  Participants will have the choice of returning two weeks later to complete study procedures.   Stopping Rules Doxazosin Participants who do not meet the criteria listed above (supine blood pressure above 100/65 mm Hg, a seated blood pressure of greater than 90/60 mm Hg, and an orthostatic change smaller than 20 mm Hg systolic or smaller than 10 mm Hg diastolic on standing) at any time during hours 2 through 6 after dosing will remain supine until the next BP assessment. Participants who do not meet the criteria above consistently from hours 2 through 6 after any dosing will not have their dose of doxazosin increased and will remain at the prior dosing level. Participants showing syncope or dizziness that does not respond to sitting down will be discharged from the study.  Stopping Criteria for Further Participation Participants who do not meet the requirements for dosing increase for 6 days will have medication discontinued and they will be discontinued from the study.  Cocaine Cocaine will not be administered if there are clinically significant arrhythmias or if vital signs are outside of acceptable ranges, which are resting pulse below 90 bpm and blood pressure below 150mm Hg systolic and 90mm Hg diastolic. In addition, repeated doses of cocaine will not be administered (and the study physician will halt continued cocaine delivery) if there are behavioral manifestations of cocaine toxicity (agitation, psychosis, inability to cooperate with study procedures).   Stopping Criteria for Further Participation Subject participation will be terminated if any of the following events occur: 1. Systolic BP above 180 mm Hg sustained for 5 minutes or more; 2. Diastolic BP above 120 mm Hg sustained for 5 minutes or more; 3. Heart rate above (220 – age x 0.85) bpm sustained for 5 minutes or more. Note: if a single value exceeding the values above is detected, the readings will be repeated until it is determined whether or not the stopping criteria have been met.  Adverse event assessment and management. We will assess participants’ well-being daily. Spontaneously reported symptoms or complaints will be recorded and reported to the IRB and NIDA and the FDA if events are classified as serious. Specific guidelines have been developed to guide assessment and intervention in the event of cardiovascular toxicity, such as malignant hypertension, ventricular arrhythmia, chest pain, etc., and are in use for our other studies involving cocaine administration. These guidelines are intended to support rather than supersede clinical judgment. If needed, a code team responds. Participants needing to be transferred to a medical or ICU ward can be, though this has never been necessary.   Assessments see attached | | --- | --- | | |

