| | Describe and assess any potential risks/discomforts and assess the likelihood and seriousness of such risks: | | --- | | |  | Potential risks of the study are those conferred by administration of doxazosin, administration of cocaine, and administration of the combination of the two. Other risks include those associated with residence on the research commons such as inadvertent breach of confidentiality.   Risks of Study drugs: Risks of cocaine; The risks from cocaine are raised or lowered blood pressure and heart rate, tremors, vomiting, convulsions, stroke, myocardial infarction, and in very rare instances, possibly death. If taken in high doses, cocaine can cause paranoia and delusions, but if taken in the doses used in this study, these effects are uncommon. The most frequent effects are changes in blood pressure and heart rate; the other effects are quite rare.   Risks associated with doxazosin administration; Dizziness, headache, drowsiness, lack of energy, weakness, palpitations, and nausea. In most instances side effects have disappeared with continued therapy or have been tolerated with no decrease in dose of drug. Less frequent adverse reactions which are reported to occur in 1-4% of patients are: Gastrointestinal: vomiting, diarrhea, constipation. Cardiovascular: edema, orthostatic hypotension, dyspnea, syncope. Central Nervous System: vertigo, depression, nervousness. Dermatologic: rash. Genitourinary: urinary frequency. EENT: blurred vision, reddened sclera, epistaxis, dry mouth, nasal congestion.  Risks of placebo administration; There are no known serious health risks to treatment with placebo.  Risks of Blood Collection The risks of inserting a needle into a vein may involve (1) pain from insertion of the needle; (2) lightheadedness; (3) fainting; (4) hematoma (like a bruise) at the site of the needle insertion; (5) inflammation of the vein; (6) clotting of the vein; (7) rarely, infection where the needle enters the skin, or (8) rarely, an allergic reaction to the tape applied afterwards.  Risks of ECG recording ECG recordings are safe. Some people may develop mild irritation due to the adhesive used to hold the electrodes on. The gel may also require washing your hands and chest after the study. Rarely, there may be an allergic reaction to ECG electrode adhesive, which might result in redness or swelling.  Other Risks and Discomforts   Some people get depressed after they stop using cocaine. Subjects will be monitored closely for symptoms of depression. The study team consists of psychiatrists and physicians who are all experienced in the field of drug abuse and they can provide counseling and/or medications if necessary. If subjects demonstrate severe depression, appropriate medical action will be taken to keep the subject safe. He/she may need to leave the study and will be referred to appropriate care, if they wish. No subjects with severe depressive symptomatology will be allowed to leave the hospital until it is established that they are safe (i.e., no suicidal ideation is present).  During the entry visit patients will be asked questions about their medical history and lifestyle and drug use. Some of these questions may be personal, and patients may feel uncomfortable or embarrassed. The questions will be asked in a private room such that no one besides the study staff will know the answers.  There is the risk of unauthorized disclosure of confidential information and possible unwanted encounters with friends or acqaintances in the treatment setting.  Visits to the study center for study procedures may be time consuming and inconvenient. Participation in the study will last about 28 days.  There may be risks and discomforts associated with participation in this study which are currently unforeseeable  Minimizing Risks: Subjects will be given a complete physical exam and medical history at entry to determine any reason why the study procedures should not be administered. Subjects will be instructed in the consent form and verbally to immediately report any adverse experiences that may arise. Subjectswill be instructed verbally and in the consent form to report any changes in concurrent medications and to check with their primary care physicians for any reasons they should not enter or continue on the study. Study sites will forward any and all adverse reactions information to the sponsor for analysis.  Cocaine is a strong sympathomimetic and has been associated with adverse cardiovascular events, including myocardial infarction and stroke, when taken illicitly. While these consequences have never been observed following controlled experimental administration, we will limit these potential risks in several ways: we will enroll only physically healthy subjects with no evidence of cardiovascular disease; we will administer relatively small doses of cocaine (up to 40mg); and we will monitor subjects closely in a medical hospital throughout the duration of action of the drug; and we have an intervention plan in place to deal with any adverse events that may occur.  We have extensive experience safely administering individual doses of 40mg cocaine. These doses are modest compared to amounts that participants in these studies have reported using daily; typical daily dosing patterns are on average 250mg to 500mg or more. Based on evidence from other laboratories, the risks associated with repeated cocaine administration are not substantially greater than those produced by single doses (Ward et al 1997a; Ward et al 1997b). The mechanisms that limit cardiovascular responses following repeated dosing are not known, but probably involve the development of acute tolerance to the cardiovascular effects of cocaine. We will carefully monitor participants and will not administer additional doses of cocaine until cardiovascular parameters have returned to preset limits, further safeguarding subjects. In the unlikely event that a subject experiences a medical emergency, the research commons is prepared to respond to any situation that may arise. It is located 5th floor of MEDVAC near [name] office. The general and psychiatric emergency rooms are located minutes away on the 1st floor of the hospital. There is a 24-hour medical emergency code team in the hospital. There is a 24-hour medical emergency code team in the hospital. A fully equipped crash cart is located on the unit.  It is our standard to obtain ECGs during screening, upon admission, and prior to discharge. [name] will monitor all ECGs. He has ACLS certification and has 14 years experience monitoring ECGs for studies involving cocaine administration.   Safety data will be reviewed regularly by a data and safety monitoring board. The board will be blinded to subjects' actual treatment assignments for the safety data. Reports from the DSMB will be sent to the site investigator for transmission to the appropriate IRB, in accordance with NIH policy.  Strict go/no-go criteria will be utilized for the infusions, and before and after each challenge session, subjects will be monitored using continuous heart rate, blood pressure, and EKG readings.  If suicidal ideation is identified in any subjects, the study physician will be contacted immediately and meet with the subject within one hour. If the participant expresses having a plan or has a history of previous suicide attempts, the subject will not be left alone until a study physician has met with him/her. If no physician is available 911 will be called to assess the situation. The studyphysician will determine the severity of the subject's suicidal intentions. If the study physician feels that the subject's risks are low then s/he will be given referrals to counselors, hotlines and clinics where s/he can seek further help. However, if the study physician determines that the subject's suicidal risks are high, he/she will develop a plan for safety with the subject, including but not limited to: contacting the participant's personal physician, encouraging the subjects to confide in family members or close friends,giving suicide hotline information, and providing appropriate referrals.  Sterile techniques will be utilized for blood draws and injections. Standard nursing techniques will be used to make the subjects as comfortable as possible. The entry visit interview will be administered in private with the utmost sensitivity to the subject. Prior to discharge an MD will evaluate the patients' medical (including vitals) and psychiatric status and determine if it is safe for them to be discharged. | | --- | --- | | |

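### Internal inconsistency in a safety threshold: F1 sets the limits for starting cocaine at 130 bpm and 165/100 mm Hg, while F2 twice sets 90 bpm and 150/90 mm Hg

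*Protocol*

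**What the plan says.** The protocol gives vital-sign limits for cocaine dosing in three places.

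- **F1, Exclusion Criteria field, under Stopping Criteria.** Cocaine is not to be initiated if there is a significant arrhythmia or if vital signs are outside the acceptable ranges, "which are resting pulse < 130 bpm and blood pressure below 165mm Hg systolic and 100mm Hg diastolic".
- **F2 Procedure, Day 10.** A check is required just before each infusion: "resting pulse must be < 90 bpm and the blood pressure must be < 150 mmHg systolic and < 90 mmHg diastolic immediately prior".
- **F2 Procedure, Stopping Rules, Cocaine.** In a sentence built almost exactly like the one in F1, the acceptable ranges are those "which are resting pulse below 90 bpm and blood pressure below 150mm Hg systolic and 90mm Hg diastolic".

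Three other statements bear on the point.

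- Inclusion criterion 5 in F1 requires "a seated blood pressure of > 90/60 mm Hg and < 150/90 mm Hg" and adds: "Resting pulse must be < 90 bpm".
- The Day 10 text also says: "Vital signs must remain within values specified under Stopping Criteria for initiation of cocaine administration". It names no section and gives no values.
- H1, in its account of how risks are minimised, states: "Strict go/no-go criteria will be utilized for the infusions". It gives no figures there. Its separate remark that further doses wait until cardiovascular values are back within preset limits gives none either.

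**The concern.** One term, the acceptable range for giving cocaine, has two numerical definitions in one document. Each passage presents its own numbers as the range, and neither refers the reader to the other. Someone working from F1 alone would take 129 bpm and 164/99 mm Hg as acceptable for starting an infusion. F2 forbids dosing at those values, and criterion 5 would have refused entry at them.

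Safety is the primary objective in Section D. Participants receive intravenous cocaine with no prospect of direct benefit, and H1 relies on the go/no-go gate as a safeguard. A gate printed with two sets of values is a weak safeguard and cannot be audited cleanly. What is at stake is participant safety and protocol compliance. No loss of power or selection effect is claimed.

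**Working it through.** No sample-size or power figure is involved. The check is a comparison of texts, some subtraction and one count.

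**Step 1. Limits side by side**

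| Measure | F1 Stopping Criteria | F2 Day 10 | F2 Cocaine stopping rule | F1 entry, criterion 5 | Gap, F1 Stopping Criteria minus F2 |
|---|---|---|---|---|---|
| Resting pulse (bpm) | < 130 | < 90 | < 90 | < 90 | 130 − 90 = 40 |
| Systolic (mm Hg) | < 165 | < 150 | < 150 | < 150 (seated) | 165 − 150 = 15 |
| Diastolic (mm Hg) | < 100 | < 90 | < 90 | < 90 (seated) | 100 − 90 = 10 |

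Three of the four statements agree. The F1 Stopping Criteria stand alone.

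**Step 2. Where the two rules disagree.** In whole-number readings they differ when every value is within the F1 limits and at least one lies in these bands: pulse 90 to 129, systolic 150 to 164, diastolic 90 to 99. Take 100 bpm and 155/95. Under F1, 100 < 130, 155 < 165 and 95 < 100, so all three pass. Under F2, 100 ≥ 90, 155 ≥ 150 and 95 ≥ 90, so all three fail.

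**Step 3. Does any text reconcile them?**

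- *First dose against repeat dose.* F1 speaks of initiating cocaine. F2 speaks of the moment before dosing and of any administration. Both therefore cover the start of dosing, and no sentence reserves the looser set for later doses.
- *The Day 10 cross-reference.* Its heading and wording fit F1 best, but it could mean F2's own rule. It can also be read as a pre-dose gate or as a continuing limit during the session. It settles nothing.
- *H1.* It gives no numbers for its go/no-go criteria, so it cannot decide between the sets.
- *Criteria for ending participation.* These (above 180 mm Hg systolic or 120 mm Hg diastolic for 5 minutes or more, and the heart-rate formula) are the same in F1 and F2. The conflict is confined to the limits for giving cocaine.

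**Step 4. How many decisions are affected.** The F1 limits attach to initiation, so the conflict is certain at one decision per session: the first infusion or, if saline comes first and the rule is read literally, the first cocaine infusion. With two phases, 1 × 2 = 2 decisions per two-phase completer. For the 20 completers planned in F1, 2 × 20 = 40. Later infusions are affected only if *initiated* is read as covering each dose.

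The figure of 40 describes 20 people who complete both phases. It is not an upper bound, because G1 allows up to 30 to be enrolled and non-completers may also be infused. Nor is it a count of actual conflicts. The documents give no basis for estimating how many readings would fall in the disputed bands.

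**The case against.** The strongest reply is that the two rules are compatible. Each says when cocaine will not be given, so staff can obey both, and the stricter set then binds. The stricter limits also appear where dosing is described, in the Day 10 procedure and in the Cocaine stopping rule, while the looser figures sit in an eligibility field. A study physician gives the infusions, an ACLS-certified physician is present, ECG is continuous, and blood pressure is checked often.

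Most of this stands, and it limits the point. A reader might infer that the protocol allows cocaine at, say, 120 bpm and 160/95. It does not: F1 never says that cocaine may be given whenever its limits are met, and infusing at those values would breach F2. A reader might also infer that every infusion is subject to conflicting rules. The text does not establish that, because F1 refers to initiation and its sentence on repeated doses concerns only behavioural toxicity.

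The reply does not remove the inconsistency. F1 calls its numbers the acceptable ranges, nothing tells the reader to look for tighter ones, and the Day 10 cross-reference may send staff back to F1. Monitoring and attendance by physicians help manage an event after dosing; they do not say which pre-dose threshold is correct.

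**Conclusion.** The point holds as an internal inconsistency: a safety threshold is wrong as written in F1. The F1 limits exceed those in F2 by 40 bpm, 15 mm Hg systolic and 10 mm Hg diastolic. Treating F1 as the error rests on F2 giving the stricter values twice and on the entry limits matching them. The conflict is certain at 40 dosing decisions for 20 two-phase completers, assuming one initiation decision per session.

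The tempting reading that the Day 10 cross-reference brings the looser limits into the dosing procedure is possible but not established, and the conclusion does not depend on it. This is not a questionable design choice. It should be corrected because the gate protects participants and the correction costs almost nothing.

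**What to change.** 1. In F1, Stopping Criteria, replace the limits for initiating cocaine with resting pulse < 90 bpm and blood pressure < 150/90 mm Hg.
2. State that this pre-dose gate applies before each infusion (20 mg, 40 mg and saline), as the Day 10 text already implies.
3. Reword the Day 10 sentence on vital signs remaining within the stopping-criteria values so that it refers to the pre-dose gate only. Any separate in-session limit is for the sponsor's clinicians to set and label. The 90 bpm and 150/90 values should not become a continuing limit after cocaine is given, since H1 says of cocaine: "The most frequent effects are changes in blood pressure and heart rate".

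The cost is one corrected sentence in F1, a statement of scope and one reworded sentence in F2. Design, sample size and analysis are unchanged. Some later doses may be delayed or withheld, but F2 already requires that.
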